## Abstract

**Background:**

Depression is an often underdiagnosed and, therefore, untreated comorbidity for low-income, racially or ethnically diverse patients with a chronic illness such as diabetes. Recent updates from the US Preventive Services Task Force guidelines in 2016 recommend depression screening for every adult but does not suggest the mode of assessment. Short message service (SMS) text messaging is an inexpensive, private, and scalable approach to provide depression screening and monitoring; it can also alleviate many barriers, such as transportation, childcare, and clinical visit time faced by the low-income population, in receiving a diagnosis of depression. Current evidence is inconsistent in comparing technology-mediated assessment versus interviewer (INTW) assessment in collecting sensitive health information, as some studies suggest that technology encourages self-disclosure while the other studies show the opposite effect.

**Objective:**

The proposed study will test the use of SMS text messaging to assess depression and its related conditions, including functional disability, pain, and anxiety, in low-income, culturally diverse, safety-net primary care populations with diabetes. The study will examine the concordance between SMS text message and interviewer assessments and evaluate test-retest reliability.

**Methods:**

The proposed study will adopt a randomized design with 200 patients assigned to four study groups: SMS/INTW, INTW/SMS, SMS/SMS, and INTW/INTW. The first two groups will be used to examine the concordance between SMS text message and interviewer assessments. The third and fourth groups will be used to evaluate test-retest reliability. Participants of the study will be recruited from the participants of the prior Diabetes-Depression Care-management Adoption Trial, a large comparative effectiveness research trial in collaboration with the Los Angeles County Department of Health Services. Test-retest reliability and concordance between SMS text message and interviewer assessments will be evaluated by the interclass correlation coefficient and the kappa statistic. Missing data patterns will be explored to understand whether participants are willing to self-disclose information related to depression in SMS text message assessments.

**Results:**

Recruitment of participants was conducted from June 2017 to November 2017. A total of 206 participants were enrolled: 52 (25.2%) in SMS/INTW, 53 (25.7%) in SMS/SMS, 49 (23.8%) in INTW/SMS, and 52 (25.2%) in INTW/INTW. The average age of the participants was 57.1 years (SD 9.2). A total of 57.8% (119/206) of participants were female, 93.2% (192/206) were Latino, and 77.7% (160/206) chose Spanish as their preferred language. Analysis of the SMS text message assessment shows the cost of distributing the 16 questions is about US $0.50 per person per assessment. Full results of the study will be reported elsewhere.

**Conclusions:**

This study is anticipated to establish the feasibility of using SMS text messaging to assess depression and its related conditions in low-income, culturally diverse, safety-net primary care populations with diabetes. We also expect to generate knowledge about whether patients in the targeted population are willing to reply and self-disclose sensitive information about depression and its related conditions through SMS text message assessments.

**International Registered Report Identifier (IRRID):**

DERR1-10.2196/12392

## Introduction

Depression is an underdiagnosed comorbidity for those with chronic illness [1] that impairs functional status and worsens outcomes, including morbidity, mortality, and health care costs [2-5]. Diabetes doubles the risk of depression relative to the general population [6,7], but as high as 50% of comorbid depression in patients with diabetes is undiagnosed and thus untreated [1]. Low-income, ethnically diverse patients with chronic illnesses are exposed to even higher risk of depression [7-9]. Hispanics have a higher prevalence of diabetes compared with non-Hispanic whites [10] and are less likely to meet hemoglobin A1c and cholesterol goals [11]. Hispanics are less than half as likely as non-Hispanic whites to receive any depression care, including guideline-level depression care [12].

Depression screening is an effective approach to reduce the rate of undiagnosed depression and thus provides timely treatment for patients [13]. As growing evidence suggests the benefits from depression screening are significant and the harms are minimal, the US Preventive Services Task Force updated its guidelines in 2016 that, for the first time in history, recommend providing screening of depression for every adult [13].

Still, significant barriers exist in adopting depression screening among low-income, ethnically diverse patients with chronic illness. This patient population often prefers safety-net primary care over specialty psychiatric care to seek mental health care. However, safety-net primary care providers often find themselves lacking the time and resources to address mental health issues on top of managing other medical conditions like diabetes [14-17]. Concurrently, minority patients are less likely to voluntarily report depressive symptoms, may view depression as a moral weakness or character flaw (ie, not an illness), and may be more likely to ascribe symptoms of depression to a physical illness [18]. Therefore, low-income, predominantly minority patients in safety-net care systems often miss out on screening and diagnosis for depression [15,19].

The proposed study will test the use of short message service (SMS) text messaging to assess depression and its related conditions, including functional disability, pain, and anxiety, in low-income, ethnically and racially diverse safety-net primary care populations. Text messaging is a highly prevalent and global phenomenon; among the 4 billion mobile phones in use, 3.05 billion, or 75%, are SMS enabled [20]. In the United States, texting among adult mobile phone users is higher among Hispanics and Latinos (83%) than among non-Hispanic whites (70%) [21]. SMS text messaging is also inexpensive, private, and can be scaled to large populations [20,21]. Thus, SMS text messaging could be an ideal approach for conducting depression screening and monitoring in underserved, ethnically and racially diverse populations.

The proposed study will test the use of SMS text messaging, in both English and Spanish, to administer the 8-item Patient Health Questionnaire (PHQ-8) assessment for depression. The Patient Health Questionnaire (PHQ) is a well-validated and widely used depression assessment tool in primary care and the general population [22-24]. Prior studies have shown that the PHQ can be reliably carried out over the telephone by interviewers [25]. However, to the best or our knowledge, no prior studies have evaluated the assessment of the PHQ using SMS text messaging in a safety-net primary care population. In addition, this is the first study to test SMS text messaging assessment for highly comorbid conditions of depression, including anxiety [26], functional disability [8], and pain [27].

## Methods

### Overall Design

The proposed study aims to recruit 200 patients randomly assigned to one of the four study groups: SMS/interviewer (INTW), INTW/SMS, SMS/SMS, or INTW/INTW. The first two groups will be used to examine the concordance between SMS and interviewer assessments for depression and its related comorbid conditions, including anxiety, functional disability, and pain. The third and fourth groups will be used to evaluate test-retest reliability. Depression assessment will be carried out using the PHQ-8, a widely used depression assessment tool in primary care and general populations [28]. The first two questions of the PHQ-8 are often used for brief assessment of depression and are known as the 2-item PHQ (PHQ-2) [28]. Anxiety will be assessed using the 2-item Generalized Anxiety Disorder scale (GAD-2) [29]. Functional disability will be assessed using the 3-item Sheehan Disability Scale (SDS) [30]. Pain will be assessed by the presence of chronic pain, pain level, and pain interference. Validity of interviewer assessments for the PHQ, SDS, and GAD-2 have been established in prior studies [25,28-30]. By completing the specific aim of this study, we expect to generate data and results that could be used to examine the validity and reliability of SMS text messaging assessment for depression and its related conditions in a safety-net primary care population with diabetes.

### Recruitment

Participants of this study will be recruited from the group of participants from the prior Diabetes-Depression Care-management Adoption Trial (DCAT), a large, US Department of Health and Human Services-funded translational study conducted from 2010 to 2013 [15,31-37]. These patients will be chosen from the DCAT because of the prior contacts and rapport built during the DCAT so that this study can fit within the short timeline of the funding requirements. The DCAT was a comparative effectiveness research trial with three study arms in collaboration with eight safety-net primary care clinics of the Los Angeles County Department of Health Services, the second-largest safety-net system in the United States. The DCAT tested an automatic telephone depression-monitoring system to facilitate collaborative depression care in patients with type 2 diabetes. A bilingual recruiter and interviewer from the DCAT will join the proposed study and will contact the participants in the DCAT technology-facilitated care (TC) group for recruitment. Participants in the DCAT TC group received regular depression monitoring every 3 or 6 months over automatic telephone calls during the DCAT. For those who agree to participate, a random number generator will be used to randomize the patients into one of the four study groups. Participants assigned to the INTW/SMS and INTW/INTW groups will receive assessments over the telephone immediately after they agree to participate. Participants assigned to the SMS/INTW and SMS/SMS groups will be notified that an SMS text message assessment will be sent to them within 48 hours.

### Sample Size Determination

Unfortunately, there is no consensus in methods to determine the sample size a priori for studying concordance, validity, and reliability [38,39]. Well-received published studies that evaluated the PHQ and SDS in primary care with interviewer assessment typically had a sample size that ranged from 100 to over 3000 [22-23,25,30]. A widely cited study that evaluated the concordance and test-retest reliability of interviewer assessments carried out over the telephone versus in person for the PHQ had a sample size about 350 [25]. Based on the sample size of previous studies, we suggest that a sample size of 200 would be appropriate, given the limit of our funding, while we acknowledge that a sample size over 1000 would be ideal to produce more reliable results. This study will aim to recruit and study 50 patients in each of the four study groups. As mentioned above, we will first recruit patients from the DCAT TC group (N=442), since these patients are more familiar with technology-mediated assessment for the PHQ. If the number of participants recruited from the TC group is smaller than the targeted sample size (ie, 50 in each of the four study groups), patients will be recruited from the other two study arms in the DCAT, namely the usual care group (N=484) and the supported care group (N=480).

### Design of the Text Messaging Assessment

The SMS text messaging assessment will include 16 questions, delivered in the order of the GAD-2, the PHQ-8, the SDS, and pain assessments (see Table 1). The 16 questions will be sent one at a time. After the participant answers a question by texting back the one number that best describes their feelings, the next message will be sent. The questions are numbered as “1 of 16, 2 of 16...” for participants to track their progress. Since SMS text messaging only supports the delivery of plain text, we use the asterisk sign (ie, *) to highlight the important part of a text message. A sample SMS text messaging assessment question is shown in Figure 1. The SMS text messaging assessment is available in both English and Spanish and implemented using the Qualtrics SMS Distribution module [40].

### Randomization and Data Collection Plan

The randomization and data collection plan is diagramed in Figure 2. After screening for eligibility and obtaining verbal consent to participate, participants will be randomized to one of the four study groups: SMS/INTW, INTW/SMS, SMS/SMS, or INTW/INTW. For all participants, measures on the following characteristics will be collected by a bilingual (ie, English and Spanish) interviewer:

Demographics: age, gender, race and ethnicity, language, marital status, education, and insurance.Personality: Ten Item Personality Measure (TIPI) of the Big Five Personality [41].Cognitive diathesis to depression: 9-item Dysfunctional Attitudes Scale (DAS) Short Form [42].Depression stigma: Depression Stigma Scale (DSS) [43].Mobile phone, Internet, and social media use.Depression history and treatment.

The above participant characteristics will be measured because evidence has suggested that demographics such as gender, personality dimensions such as extraversion, dysfunctional attitudes that exist in individuals with depression, and technology use can influence self-disclosure of sensitive health information [44-46]. Measuring these characteristics is critical for determining the generalizability of the proposed study.

Following the collection of characteristics, participants in the SMS/INTW group will first receive the SMS text message assessment within 48 hours. Within 7 days following the SMS text message assessment, the interviewer will contact the participant over the telephone to repeat the same assessment. Participants in the INTW/SMS group will first answer the interviewer assessment over the telephone; they will then reply to the SMS text message assessment within a 7-day period. Participants in the SMS/SMS and INTW/INTW groups will receive two SMS text messages and two interviewer assessments, respectively, within a 7-day period. The choice of interval between the two assessments (ie, 7 days) is based on a prior study that compares interviewer assessment carried out over the telephone versus in-person assessment of depression [25]. A shorter interval is likely to increase the likelihood of repeating the answer from the first assessment in the subsequent one, while a longer interval will increase the probability of change in real severity of depression.

**Table 1 table1:** Text messages and their response options for assessing depression and related conditions. Asterisks highlight the important part of the text message.

Module and text message		Response options

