**Pain**		
	14 of 16. Have you had pain that has been present most of the time for 6 months or more during the past year?	1: Yes; 2: No; 3: Don’t know
	15 of 16. During the past 4 weeks, how much did pain interfere with your normal work, including both work outside the home and housework?	1: Not at all; 2: A little bit; 3: Moderately; 4: Quite a bit; 5: Extremely; 6: Don’t know
	16 of 16. Please rate your pain by telling us the one number that best describes your pain at its WORST in the last 24 hours (0: No pain; 10: Pain as bad as you can imagine).	Score from 0-10, where 0 means *No pain* and 10 means *Pain as bad as you can imagine*

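### The retest rule caps the gap at 7 days but sets no minimum, so it does not deliver the 7-day interval that the protocol describes and defends

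*Protocol article*

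**What the plan says.** The Randomization and Data Collection Plan section of the Protocol article sets the timing group by group.

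- SMS/INTW: "Within 7 days following the SMS text message assessment, the interviewer will contact the participant over the telephone to repeat the same assessment".
- INTW/SMS, after the interview: "they will then reply to the SMS text message assessment within a 7-day period".
- The two same-mode groups: "Participants in the SMS/SMS and INTW/INTW groups will receive two SMS text messages and two interviewer assessments, respectively, within a 7-day period".

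The first assessment also starts at different times. The plan says that "participants in the SMS/INTW group will first receive the SMS text message assessment within 48 hours", while the Recruitment section has the interviewer-first groups assessed by telephone as soon as they agree.

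The paragraph then justifies the timing: "The choice of interval between the two assessments (ie, 7 days) is based on a prior study". It argues from both sides. On one side: "A shorter interval is likely to increase the likelihood of repeating the answer from the first assessment in the subsequent one". On the other, "a longer interval will increase the probability of change in real severity of depression".

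The recall periods are in Table 1: two weeks for GAD-2 and PHQ-8, a month for the SDS and four weeks for pain interference (item 15). Item 16 asks for the number that best "describes your pain at its WORST in the last 24 hours".

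The Statistical Analysis section measures concordance by ICC and kappa, and test-retest reliability by ICC.

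**The concern.** The justification treats the interval as a chosen length, too short being one hazard and too long the other. The operating rules control only the second hazard. Nothing in them prevents a second assessment a few hours after the first, which is the situation the authors say encourages repeated answers.

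This bears directly on the estimates. A participant who remembers and repeats an answer raises agreement without the instrument being more reliable. A very short gap also removes real change, which raises agreement again. If gaps vary freely, an ICC or kappa is an average over an unknown mix of gaps. If the mix happens to differ between groups, a difference between same-mode and cross-mode agreement could be read as an effect of mode when part of it is timing.

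Item 16 raises a separate difficulty. With so short a recall period, two assessments a day or more apart ask about different days, so some disagreement is to be expected even from a perfect instrument.

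**Working it through.** **Step 1. Does the rule give the stated interval?** The stated figure is 7 days. Set against it, the rules are:

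| Group | What the 7 days bound | Start of the period | Minimum gap |
|---|---|---|---|
| SMS/INTW | interviewer's contact | first SMS assessment | none |
| INTW/SMS | participant's reply | not stated | none |
| SMS/SMS | two messages received | not stated | none |
| INTW/INTW | two interviews | not stated | none |

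The permitted gap runs from just above 0 to 7 days. The rules are compatible with a 7-day interval but do not produce one.

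**Step 2. Does the ceiling differ between groups?** That depends on the unstated start. If the period starts at the first assessment, the ceiling is about 7 days everywhere. If it starts at enrolment, an SMS/SMS participant whose first message goes out at 48 hours has at most 7 − 2 = 5 days between messages, against 7 for an INTW/INTW participant interviewed at once.

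**Step 3. How much recall time do the two assessments share?** With recall period W and gap g, overlap = max(0, W − g)/W. W comes from Table 1; the SDS month is assumed to be 30 days.

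| Items | W | g = 1 day | g = 7 days |
|---|---|---|---|
| PHQ-8, GAD-2 | 14 days | 13/14 = 93% | 7/14 = 50% |
| Pain interference | 28 days | 27/28 = 96% | 21/28 = 75% |
| SDS | 30 days | 29/30 = 97% | 23/30 = 77% |
| Worst pain (item 16) | 1 day | 0% | 0% |

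Below one day, which the rule allows, item 16 does overlap: 21/24 = 87.5% at 3 hours and 12/24 = 50% at 12 hours. From 24 hours on, the overlap is zero.

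**Step 4. Could this matter for the coefficients?** The document gives no reliability, rate of change or memory effect, so this step is illustration only. Take

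r(g) = R × ρ^(g/7) + (1 − R) × m × exp(−g/2),

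where g is in days, R is the reliability, ρ the true-score correlation over 7 days, and m the share of the error part that is remembered at first. Assume R = 0.8, ρ from 0.80 to 0.95 and m from 0.3 to 0.6.

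- At 6 hours (g = 0.25), r is about 0.85 to 0.90.
- At 7 days, r is about 0.64 to 0.76.

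For ρ = 0.9 and m = 0.3 the parts are 0.797 + 0.053 = 0.850 at 6 hours and 0.720 + 0.002 = 0.722 at 7 days. So in this example both more real change and less memory contribute to the fall. The figures show that a material shift is possible; they do not estimate it for this trial.

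**The case against.** The strongest reply is that the 7 days in the justification is shorthand for the window just described, so the text is loose rather than contradictory. The safety plan's reference to an assessment week fits that reading. It is a fair one, and two incompatible numbers should not be alleged. It does not dispose of the point: read as a ceiling, the rule guards only against real change and leaves uncontrolled the repetition that the authors themselves raise.

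A second reply is that Figure 2 is not shown and that a condensed article leaves scheduling detail to the full protocol. That is right for call lists and message timing. The point here is narrower: the article states both a rule and a reason for it, and the rule does not secure what the reason asks for.

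Several stronger readings are tempting, and the document does not support them:

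- A reader might infer that the rule differs by group. All four share a 7-day cap and none has a minimum; the ceilings differ only if the unstated start is enrolment.
- A reader might infer that gaps will be systematically shorter in one mode, because messages can be timed and telephone contact cannot. The article does not say when second messages go out, how second calls are scheduled or what gaps occurred.
- A reader might infer that the interval was chosen solely to avoid repeated answers. The text gives a trade-off and attributes the choice to a prior study.
- A reader might infer that disagreement on item 16 is all real change. It will include real change, along with response error and any mode effect.

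**Conclusion.** The point holds in a limited form. The protocol describes a 7-day interval and argues against shorter ones, but its rules set only a maximum and name the start of the period for one group of four. A same-day retest complies. ICC and kappa, same-mode and cross-mode, can therefore partly reflect memory and timing. This should be corrected; it does not invalidate the design.

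The size of the effect on the coefficients is unknown. Shared recall time measures how different the permitted conditions are; it is not a bias. A difference in gaps between groups is possible but not shown. For item 16, the absence of shared recall time at 24 hours or more follows from the item's wording alone, and it affects one item of 16.

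**What to change.** Reconcile the rule with the stated interval. Use one anchor in all four groups, completion of the first assessment, with a lower as well as an upper bound. A window of 5 to 7 days is one workable choice; the document gives no source for a particular lower bound. Record the actual gap and report its distribution by group. Repeat ICC and kappa restricted to the window or adjusted for gap. For item 16, interpret cross-mode agreement only relative to agreement in SMS/SMS and INTW/INTW, which the design already provides.

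The cost is a scheduling rule, a small added analysis and some second assessments outside the window. Loss among telephone retests should not be assumed to be trivial: the Results section reports 490 of 769 recruitment call attempts (63.7%) as unsuccessful, although those were first contacts from an old list and not calls to enrolled participants.

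The Results section also says that recruitment ended in November 2017. If data collection is complete, the scheduling change no longer applies, but the gap report, the repeated ICC and kappa, and the reading of item 16 still do, wherever assessment dates were recorded.
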